### Analysis

All analyses will be on an intention-to-treat basis.

The primary outcome will be physical fatigue as measured by the physical fatigue domain of the MFI-20 at four weeks post operatively. If the primary outcome is normally distributed it will be compared using a *t*-test, ANCOVA adjusting for the minimization factors (primary analysis) and ANCOVA with further adjustment for prognostic factors.

Physical fatigue will also be compared at three and six months, the remaining quality of life variables at 4 weeks, 3 and 6 months, and the cosmetic outcome at 6 and 12 months, using the same analyses as for the primary outcome. Physical fatigue will be adjusted for the level of physical fatigue prior to surgery. The other measures of fatigue will also be reported.

For all continuous outcome variables, if there is severe departure from Normality the first approach will be transformation. If the data cannot be transformed to Normality, a Mann–Whitney test will be used. In the latter case no adjustment will be made for the minimization or prognostic factors.

Hospital stay will be compared using Kaplan Meier plots and log rank tests. The complications, re-operation and re-admission data will be binary and will hence be compared between the randomisation groups using a chi square test (or Fisher exact test if the data is sparse).

Quality of Life assessments at 4 weeks as measured by the SF-36 will be analysed as suggested in the SF-36 manual, comparison between treatments will use *t*-test and ANCOVA to adjust for prognostic factors. Mixed-effects models of repeated measures will be used to evaluate longitudinal comparisons (4 weeks, 3 months and 6 months).

The other four domains of the MFI will be analysed in the same way as the physical fatigue domain specified in the primary analysis.

The comparison between treatment groups of standardised performance indicators will use t-tests and ANCOVA adjusting for prognostic factors and baseline.

The tumour stage, quality of surgery grade, the physical measurements and the frequency of Dukes’ C2 cases will be compared between groups.

Analysis of the health economic data will be undertaken separately by those involved in the health economic analysis. Costs will be estimated from the perspective of the UK NHS and health benefits expressed in terms of quality-adjusted life-years (QALYs). The cases where laparoscopic surgery may be considered cost effective will be pre-defined and the mean differential costs and QALYs will be calculated in order to assess whether any of these conditions are satisfied. The relative costs of the operative and peri-operative period will be derived for all trial patients including the cost of consumables that are likely to differ between the two surgical procedures.

QALYs will be calculated for each patient in the trial, on the basis of their responses to the EQ-5D pre-operatively, at one month, three months and six months. Given that the time horizon of the analysis will be less than one year, total costs and QALYs remain undiscounted. To account for the skewed nature of the data, 95% CIs for the differential costs and QALYs will be estimated using bootstrapping methods. Missing data will be imputed using a multivariate multiple imputation procedure (Solas 3.0).

Statistical analysis will be undertaken using Stata (StataCorp LP).

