### Randomisation

Following consent, eligible patients will be randomised in a 1:1 ratio to open or laparoscopic resection using a central computer system at the Oncology Clinical Trials Office. Simple randomisation will be used for the first 50 patients then minimization with a random element (0.8) [25]. The stratification factors used in the minimization are hospital, cancer site (colon/rectum) and age (<66 years, 66–75 years, >75 years). To facilitate blinding of outcome observers the randomisation allocation will be sent directly to the patient’s surgeon via email and will not be made available to the site staff member completing the randomisation process.

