### Patient reported and functional outcomes

Health related quality of life will be assessed using the SF-36 questionnaire [21]. Quality of life will also be analysed with the EQ-5D. Cosmetic outcomes will be performed using a body image assessment [23,28]. Time points for the completion of these questionnaires are shown in Table 3.

**Table 3 T3:** Time points for the collection of patient reported and functional outcome data

**Questionnaire/Assessment**	**Data Collection Time Point**				
	**Pre Operative***	**Post-operative**			
		**4 weeks**	**3 months**	**6 months**	**12 months**
MFI-20	X	X	X	X	
SF-36	X	X	X	X	
EQ-5D	X	X	X	X	
Health Economics	X	X	X	X	
Body Image	X			X	X
SPIs	X	X	X	X	

^*^ To be completed not more than 4 weeks prior to surgery.

An observer assessment of physical function will be measured using standardized, objective performance indicators (SPIs) [24] which comprise a test of lower limb strength, balance and endurance. SPIs will be measured prior to surgery and then at 4 weeks, 3 and 6 months postoperatively. The tests differs from those described by Guralnik et al., in that patients will be measured for walking speed along a 10 metre, instead of 8 foot course, with a 61.5 cm (2 foot) clear zone at each end as originally described.

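### The article does not settle whether baseline physical fatigue belongs in the primary 4-week model, and it states no baseline term for several questionnaires that are scored before surgery

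*Protocol article*

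**What the plan says.** All references are to the protocol article.

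- **Analysis, primary outcome.** Physical fatigue at four weeks is to be compared by a t-test and by "ANCOVA adjusting for the minimization factors (primary analysis) and ANCOVA with further adjustment for prognostic factors". Only the middle of these three comparisons is marked as primary.
- **Randomisation.** "The stratification factors used in the minimization are hospital, cancer site (colon/rectum) and age", with age in three bands. Baseline fatigue is not a minimization factor.
- **Analysis, next paragraph.** Physical fatigue at three and six months, the remaining quality of life variables and the cosmetic outcome are to be compared "using the same analyses as for the primary outcome". The following sentence reads "Physical fatigue will be adjusted for the level of physical fatigue prior to surgery".
- **Analysis, other outcomes.** The other four MFI-20 domains "will be analysed in the same way as the physical fatigue domain specified in the primary analysis". For SF-36, "Quality of Life assessments at 4 weeks as measured by the SF-36 will be analysed as suggested in the SF-36 manual", with a t-test and an ANCOVA on prognostic factors. The standardised performance indicators are to have "ANCOVA adjusting for prognostic factors and baseline".
- **Table 3.** MFI-20, SF-36, body image and the performance indicators are all scheduled pre-operatively. The footnote reads "To be completed not more than 4 weeks prior to surgery".

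**The concern.** The primary model should follow from one reading of the text, and here it does not. An analyst could fit the 4-week model with or without baseline fatigue and point to a sentence in the article for either choice. Unless a fuller document fixes the model, that choice could be made after the data are seen.

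Two further things are at stake. The first is precision: a pre-operative score on the same scale usually explains part of the variation in the later score, and leaving it out forgoes that gain. The second is chance imbalance. Baseline fatigue is not balanced by the minimization, and the first 50 patients are allocated by simple randomisation, so a difference between arms at baseline can carry into an estimate that does not adjust for it.

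The question also spreads. The other MFI-20 domains take their specification from the primary one, and SF-36 and body image are sent through the primary-outcome analyses. Whatever is unclear for physical fatigue is unclear for them, and none has a baseline sentence of its own.

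**Working it through.** **1. The two readings of the baseline sentence**

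| Reading | Consequence |
|---|---|
| It covers every time point, including 4 weeks | The covariate list beside the primary label is incomplete: it should be hospital, cancer site, age and baseline fatigue |
| It covers 3 and 6 months only | Those analyses are not the same as the primary one, contrary to the sentence just before |

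The text is inconsistent on both. Reading the undefined term for prognostic factors as including baseline does not help. The sentence on the performance indicators names baseline separately from prognostic factors, and a baseline term placed there would enter only the third comparison, which is not the primary one.

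**2. Reproducing the stated sample size**

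Inputs (Statistical analysis, sample size): difference 0.45 SD, two-sided 5%, loss to follow-up 15%, conversion 8%.

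Formula: n per arm = 2(z₀.₉₇₅ + z_power)² / 0.45², then divided by 0.85 × 0.92 = 0.782.

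- 90% power: 2(1.960 + 1.282)² / 0.2025 gives 104; 104 / 0.782 = 132.99, so 133 per arm and 266 in total, as stated.
- 80% power: 2(1.960 + 0.842)² / 0.2025 gives 78; 78 / 0.782 = 99.7, so 100 per arm and 200 in total. With the t distribution, 79 / 0.782 = 101.02, or about 101 per arm and 202 in total, as stated.

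Both totals reproduce from an unadjusted comparison of two means with no baseline covariate.

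**3. What baseline adjustment would add**

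Effective number per arm on the plan's own basis: 101 × 0.85 × 0.92 = 78.98, about 79.

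With correlation ρ between baseline and 4-week fatigue, the residual SD is √(1 − ρ²), and power ≈ Φ(0.45 √(79/2) / √(1 − ρ²) − 1.96). With no baseline term, 0.45 × √(78.98/2) = 2.828 and Φ(0.868) = 80.7%.

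The documents do not give ρ. The values below are assumptions.

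| ρ | Standard error relative to no baseline | Power |
|---|---|---|
| 0 (no baseline) | 1.00 | 80.7% |
| 0.3 | 0.95 | 84.2% |
| 0.4 | 0.92 | 87.0% |
| 0.5 | 0.87 | 90.4% |

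The minimization factors are taken to explain nothing here. If they explain some of the variation, ρ should be read as the correlation that remains after them.

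**4. Chance imbalance**

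Patients analysed per arm: 101 × 0.85 = 85.85. The standard error of the baseline difference is √(2/85.85) = 0.153 SD, so a difference beyond 1.96 × 0.153 = 0.30 SD in either direction occurs about 5% of the time. At an assumed ρ of 0.5 and equal SDs at the two visits, a 0.30 SD imbalance moves the unadjusted estimate by 0.5 × 0.30 = 0.15 SD, which is one third of the 0.45 SD target.

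**The case against.** The best defence is that the model asked for may already be the plan. The baseline sentence carries no qualifier, so it can be read as applying wherever physical fatigue is analysed. The statement that later time points share the primary analyses also favours one common model. On that reading only the placement of the sentence is awkward. This is a fair reading, but the article does not say so, and the parenthetical label remains attached to a list without baseline.

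It is also true that an ANCOVA on the minimization factors alone is valid in a randomised comparison. An analysis plan not shown here may fix the covariates. That limits the risk of a choice after the data are seen, but it does not make the article's own sentences agree.

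Three stronger readings might be inferred, and the document supports none of them:

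- **That there are two rival primary models and the weaker one was chosen.** Only one model is called primary, and which covariates were intended for it is not established.
- **That the trial is underpowered because baseline is missing.** On the plan's own basis the model without baseline has 80.7% power, which meets the stated 80%. A lower starting figure requires a separate argument that conversion dilutes the effect, and the baseline question neither needs nor settles that.
- **That SF-36 is adjusted for prognostic factors alone.** The remaining quality of life variables are also sent through the primary-outcome analyses, which include the minimization-factor ANCOVA. What is missing for SF-36 is a stated baseline term, not every other adjustment.

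**Conclusion.** The point stands as an inconsistency about one covariate in the primary model, together with unstated baseline terms for related questionnaires. It is worth correcting, but it is not a flaw in the design or in the sample size.

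The inconsistency rests on the text alone and needs no assumption. The size of the benefit does need one: power rising from about 80% to between 84% and 90% assumes a correlation of 0.3 to 0.5. The direction holds for any correlation that is not negligible. At 0.5 the gain would roughly restore the 90% power given up when recruitment was slow, with no extra patients.

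One caveat applies to the baseline itself. Surgery may take place up to 6 weeks after randomisation, and the questionnaire must be completed within 4 weeks before surgery. At the limit it is therefore filled in at least 6 − 4 = 2 weeks after allocation. Patients are to be blinded until a week after surgery or earlier discharge, so the score should not depend on the arm if blinding holds, and it remains a legitimate covariate.

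**What to change.** 1. State one primary model: 4-week physical fatigue on treatment arm, pre-operative physical fatigue, hospital, cancer site and age group. Attach the primary label to that list.
2. Label the t-test and the ANCOVA with further prognostic factors as supportive.
3. Say that the 3- and 6-month physical fatigue analyses use the same covariates, so that the claim of identical analyses is true.
4. Use the same form, with each outcome's own pre-operative score, for the other four MFI-20 domains, SF-36 and body image. For SF-36, reconcile the two sentences that give different adjustment sets.

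The cost is a few sentences, settled before the outcome data are examined. Table 3 already schedules every baseline score needed, the sample size does not change, and each model spends one further degree of freedom.

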### Statistical analysis

Sample size: The original sample size calculation required 266 patients (133 per treatment arm) to allow 90% power to detect a difference in the primary outcome of fatigue (as measured by physical fatigue domain of the MFI-20) of 0.45 standard deviations at p = 0.05 (two-sided). This includes a loss to follow up of 15% and a conversion rate of 8% from laparoscopic to open surgery. Following slower than expected recruitment the power was lowered to 80% in order to complete the study in a timely manner. With all other variables remaining the same the subsequent sample size of 202 (101 per treatment arm) is required. Additionally the study is powered to detect a 3 day difference in hospital stay at 80% power and p = 0.05 (two-sided).

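### Physical fatigue at 3 and 6 months is tested one visit at a time, leaving out the 4-week score that an already planned repeated-measures model would use; SF-36 at 4 weeks has two unreconciled covariate rules

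*Protocol article*

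**What the plan says.** All references are to the protocol article.

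- **Fatigue.** The Analysis section compares physical fatigue at 4 weeks by a t-test, by ANCOVA on the minimization factors (the primary analysis) and by ANCOVA with further prognostic factors. It then states "Physical fatigue will also be compared at three and six months", by the same analyses and with adjustment for pre-operative fatigue. The other four MFI-20 domains are treated as the physical domain is.
- **SF-36, first rule.** The same sentence sends the remaining quality of life variables, at 4 weeks, 3 and 6 months, to the primary outcome's analyses.
- **SF-36, second rule.** A later paragraph says "Quality of Life assessments at 4 weeks as measured by the SF-36 will be analysed as suggested in the SF-36 manual", with a t-test and an ANCOVA on prognostic factors. It continues: "Mixed-effects models of repeated measures will be used to evaluate longitudinal comparisons (4 weeks, 3 months and 6 months".
- **Schedule.** Table 3 collects MFI-20 and SF-36 at identical times: pre-operatively, 4 weeks, 3 months and 6 months.
- **Population and loss.** The Analysis section opens with "All analyses will be on an intention-to-treat basis". The sample size paragraph says of its total "This includes a loss to follow up of 15" per cent. The only imputation sentence stands in the text on costs and QALYs.

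**The concern.** A t-test or ANCOVA on the 6-month score alone drops every patient without that score, including those whose 4-week score is on file. Adjustment for pre-operative fatigue deals with loss that depends on the pre-operative level. It cannot deal with loss that depends on how tired the patient was at 4 weeks. If very fatigued patients return less often, and more so in one arm, the patients still seen at 3 and 6 months are no longer comparable. Such a difference between arms is conceivable, because blinding ends at day 7 or discharge, before any post-operative fatigue form in Table 3.

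A repeated-measures model keeps the 4-week score of patients lost later. It is valid when loss depends on observed values. The article already names such a model for the same visits but does not clearly apply it to fatigue.

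Separately, SF-36 at 4 weeks falls under two rules: minimization factors as the primary adjustment, or prognostic factors. At 3 and 6 months it falls under both visit-wise tests and the mixed model. Nothing says which result is the one to report, so the choice could be made after the results are known.

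**Working it through.** **1. The plan's own figure.** Inputs from the sample size paragraph: 0.45 SD, two-sided 0.05, 15% loss, 8% conversion. The first calculation "required 266 patients (133 per treatment arm) to allow 90% power"; later "the power was lowered to 80% in order to complete the study in a timely manner", giving 202 (101 per arm).

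Per arm, n = 2(z₁₋α/₂ + z₁₋β)² / 0.45², divided by (1 − 0.15)(1 − 0.08).

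- 90% power: n = 104; 104/0.85/0.92 = 132.99, so 133, as stated.
- 80% power: n = 78; 78/0.85/0.92 = 99.7, so 100. With the exact t distribution, n = 79 and 79/0.85/0.92 = 101.02, against the stated 101.

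The figures reproduce to within about one patient per arm. The 15% therefore acts as an inflation factor for the primary comparison. Loss at 3 and 6 months is not given anywhere.

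**2. The 4-week primary visit.** This is the first post-operative MFI-20 assessment. If patients who miss it do not return, a repeated-measures model has no post-operative score to add and uses the same information as a baseline-adjusted ANCOVA. If some return, it gains a little. In 600 simulated trials per scenario (15% missing at 4 weeks, assumed correlations 0.4 to 0.65), the variance of the complete-case estimate relative to the mixed model was 1.00 if none were seen later, 1.035 if half were and 1.041 if all were. The gain is 0 to 4%.

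**3. The later visits: where bias comes from.** Assume equal correlation ρ between all visits. Given the pre-operative score, the slope of the 6-month score on the 4-week score is (ρ − ρ²)/(1 − ρ²) = ρ/(1 + ρ), which is 0.23, 0.33 and 0.41 for ρ = 0.3, 0.5 and 0.7. If D is the difference between arms in the mean baseline-adjusted 4-week deviation among patients still seen, then approximately

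bias of the single-visit ANCOVA ≈ ρ/(1 + ρ) × D.

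D is zero if loss is unrelated to fatigue, small if the relation is equal in both arms, and larger if it differs. Under equal correlation the expression is the same at 3 months for the same loss.

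**4. The later visits: size.** Large-sample simulation, 1,000,000 patients per scenario. Assumptions: ρ = 0.3, 0.5 and 0.7; treatment effect −0.45 SD at 4 weeks and −0.20 SD at 6 months; overall loss 15% or 25%; log-odds of loss linear in the 4-week score. Slopes per SD (open arm, laparoscopic arm) were (0, 0); (0.5, 0.5) and (1, 1); (1, 0) and (1, −0.5). Bias at 6 months, in SD:

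| How loss relates to 4-week fatigue | 15% loss | 25% loss |
|---|---|---|
| Unrelated | −0.001 to 0.002 | 0.000 to 0.003 |
| Same in both arms | 0.001 to 0.014 | 0.001 to 0.016 |
| Differs by arm | 0.030 to 0.051 | 0.045 to 0.087 |

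An analysis that also uses the 4-week score was within 0.005 SD of zero in every scenario. Positive values mean that the laparoscopic benefit is understated, because the arm-specific scenarios lose fatigued open-arm patients. If the laparoscopic arm lost its fatigued patients instead, the sign would reverse.

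**5. Scale.** With 15% loss, 101 × 0.85 = 85.85 patients per arm remain. The unadjusted standard error of a difference is √(2/85.85) = 0.153 SD. A bias of 0.05 SD is about one third of that (0.05/0.153 = 0.33).

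**The case against.** The strongest reply is that the article never says fatigue will be analysed on available cases. A condensed article may leave missing-data handling to the full protocol or SAP, neither of which is shown. That stands as far as it goes: silence on missing scores is not the point here, and declaring intention-to-treat contradicts nothing. The point is the method the article does choose for the later visits. Without further handling, it uses only that visit's scores.

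A reader might infer that the primary endpoint is open to dropout bias. The documents do not support this. Fatigue is adjusted for its pre-operative level, there is no earlier post-operative score to exploit, and the gain at 4 weeks is 0 to 4% in variance.

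A reader might also expect large bias at the later visits. One simulation, with about 18% missing and concentrated in fatigued open-arm patients, gave −0.188 and −0.110 SD against assumed effects of −0.27 and −0.18. Those estimates are 30% and 39% too small (0.082/0.27 and 0.070/0.18). This is a single unfavourable scenario over small assumed effects, and nothing in the article makes it the expected one.

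Two readings of the wording soften the point. The mixed-model sentence does not itself name SF-36, so it might cover quality of life more widely; fatigue would then have two rules, and the text would still need to say which governs. The SF-36 sentence on prognostic factors might be a partial restatement of the primary outcome's set of analyses, and a 4-week comparison can coexist with a longitudinal model. Even so, the text does not identify the governing SF-36 adjustment.

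Finally, baseline-adjusted ANCOVA at one prespecified visit is an accepted analysis. This is accepted, and it is why the primary analysis should stay as it is.

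**Conclusion.** The point holds for the secondary 3- and 6-month MFI-20 comparisons and for the SF-36 rules, and no further. As written, fatigue at those visits is compared without the observed 4-week score, although a model that would use it is already in the plan. The avoidable bias lies between about 0 and 0.05 SD at 15% loss and reaches 0.05 to 0.09 SD at 25% only if loss depends on 4-week fatigue differently in the two arms. These figures rest on assumed correlations, an assumed dropout mechanism with loss depending on observed scores, and assumed loss at later visits. Carrying the 15% over to 3 and 6 months is itself an assumption. The sample size is unaffected. The change is worth making because it is cheap and removes a choice that could otherwise be made after the data are seen, not because a large bias has been shown.

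**What to change.** 1. Keep the 4-week ANCOVA as the primary analysis, and state that it adjusts for the minimization factors and pre-operative physical fatigue.
2. Estimate the 3- and 6-month contrasts for physical fatigue and the other MFI-20 domains from the mixed-effects repeated-measures model already planned. Fit it to 4 weeks, 3 and 6 months with treatment, visit, treatment-by-visit, baseline score by visit and the minimization factors. State that it assumes loss depends on observed values.
3. Keep the single-visit ANCOVAs at 3 and 6 months as sensitivity analyses.
4. For SF-36, state one governing model and one covariate set, and remove or subordinate the other rule.
5. Say how the Mann-Whitney fallback for severe non-normality applies where the repeated-measures model is used, since that model relies on approximate normality.

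The cost is a change of analysis wording and slightly more modelling. No new data and no change in sample size are needed.

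### If physical fatigue is severely non-Normal and cannot be transformed, the primary test becomes an unadjusted Mann–Whitney that ignores the minimisation factors, cannot use baseline fatigue and does not estimate the mean difference the trial is sized on

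*Protocol article*

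**What the plan says.** All of this is in the protocol article.

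- **Endpoint** (Analysis): "The primary outcome will be physical fatigue as measured by the physical fatigue domain of the MFI-20 at four weeks post operatively".
- **If the outcome is Normal** (Analysis): a t-test, then "ANCOVA adjusting for the minimization factors (primary analysis) and ANCOVA with further adjustment for prognostic factors".
- **If it is not** (Analysis): "For all continuous outcome variables, if there is severe departure from Normality the first approach will be transformation". Next, "If the data cannot be transformed to Normality, a Mann–Whitney test will be used". Then, "In the latter case no adjustment will be made for the minimization or prognostic factors".
- **Baseline** (Analysis): "Physical fatigue will be adjusted for the level of physical fatigue prior to surgery". This sentence is in the paragraph on the three- and six-month comparisons. The sentence defining the primary ANCOVA does not name baseline.
- **Allocation** (Randomisation): simple for the first 50 patients, then minimisation with a random element of 0.8. "The stratification factors used in the minimization are hospital, cancer site (colon/rectum) and age", the last in three bands.
- **Sample size** (Statistical analysis): 202 patients for 80% power to detect 0.45 SD at two-sided p = 0.05, with 15% loss to follow-up and 8% conversion. The earlier target was 266 patients for 90% power.
- **Baseline MFI-20** (Table 3): collected no more than 4 weeks before surgery.

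**The concern.** The primary test can take three forms: adjusted ANCOVA on the original scale, adjusted ANCOVA on a transformed scale, or an unadjusted rank test. The form depends on how the outcome is distributed. The third form departs from the rest of the design in three ways.

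1. Allocation is balanced on hospital, site and age. An analysis that ignores those factors overstates the variance of the treatment contrast when they are prognostic, so the test is conservative.
2. A Mann–Whitney test cannot use the baseline fatigue score, probably the most useful covariate available.
3. A rank test addresses a different quantity from the difference in means on which the trial was sized.

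The switch is also hardly needed. With about 86 observed patients per arm, an adjusted comparison of means is robust to moderate non-Normality, and robust or bootstrap intervals can deal with worse. Planned power has already been cut from 90% to 80%, so there is little to spare.

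**Working it through.** **1. Reproduce the sample size.** Per arm, n = 2(z₀.₉₇₅ + z_power)² / 0.45², divided by 0.85 × 0.92 = 0.782 for loss and conversion.
- 90% power: n = 103.8, so 104. 104 / 0.782 = 133.0 per arm, total 266. This matches exactly.
- 80% power: n = 77.5, so 78. 78 / 0.782 = 99.7, so 100 per arm, total 200. The t-based n of 79 gives 101.02 per arm, which is 202 to the nearest whole patient and 204 if rounded up. The stated 202 is reproduced.

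The calculation takes no credit for covariates. Expected observed patients are 101 × 0.85 = 86 per arm. The net number after both allowances is 101 × 0.782 = 79 per arm.

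**2. Large-sample power at 79 per arm.** Power = Φ(0.45 × √(m/2) − 1.96), where m is the effective number per arm.
- Unadjusted means, m = 79: Φ(2.83 − 1.96) = 80.7%.
- Mann–Whitney on Normal data (efficiency 0.955), m = 75.4: Φ(2.76 − 1.96) = 78.9%.
- Adjusted means, m = 79/(1 − R²): 82.7%, 84.6%, 87.0% and 90.4% for R² of 0.05, 0.10, 0.16 and 0.25.

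The article gives no R² and no baseline correlation, so these are ranges and not estimates. Normal data would not trigger the fallback, so step 3 uses scores that might.

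**3. Simulated power for bounded scores.** Assumptions: integer score 0–16, 79 per arm, balanced pairs standing in for minimisation, effect set to 0.45 SD, 2,500 runs per row. The Monte Carlo standard error is √(0.8 × 0.2 / 2500) = 0.8 points. Compare within rows only.

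| Pile-up | Baseline correlation / factor R² | Mann–Whitney | ANCOVA, factors | ANCOVA, factors + baseline |
|---|---|---|---|---|
| Ceiling | 0.3 / 0.05 | 77.4% | 78.5% | 81.6% |
| Ceiling | 0.5 / 0.10 | 77.2% | 79.5% | 89.6% |
| Floor | 0.3 / 0.05 | 90.8% | 90.2% | 91.9% |
| Floor | 0.5 / 0.10 | 90.2% | 90.6% | 95.5% |
| Both ends | 0.3 / 0.05 | 85.0% | 84.1% | 86.9% |
| Both ends | 0.5 / 0.10 | 84.5% | 85.8% | 92.9% |

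Against factor-only ANCOVA, Mann–Whitney runs from a loss of about 2 points to a gain of about 1. Against ANCOVA with baseline it loses about 1 to 12 points.

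**4. The stated design.** This simulation used 202 patients, the article's allocation rule, 15% loss, 8% conversion, a rounded 4–20 score (range assumed), factor R² 0.03–0.10 and baseline correlation 0.3–0.5. Power was 73–76% for Mann–Whitney, 73–80% for ANCOVA on the factors and 77–87% with baseline added. Setting by setting, the loss was about 0–4 points against the first ANCOVA and about 3–13 points against the second.

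**5. Strong unbounded skew.** For exponential and lognormal outcomes at correlation 0.3, Mann–Whitney reached 92–97%, against 81–82% (factors) and 84–85% (with baseline). At correlation 0.5 it reached 88.2% and 91.4%: above factor-only ANCOVA (83.3% and 84.5%), but below ANCOVA with baseline (93.5% and 93.3%).

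**6. Type I error.** With factor R² 0.10, Mann–Whitney rejected in 3.4–4.2% of null trials in the paired simulation. In the stated-design runs it rejected in about 3.3–4.2%, against 4.3–5.2% for ANCOVA. Allowing for the spread across runs, about 3–4.5% is a fair range. At these rates the Monte Carlo error with 2,500 runs is about 0.4 points.

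**The case against.** Most of the opposing case stands, and it limits the point.

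- **The trigger is narrow.** A reader might infer that any non-Normality sends the primary test to Mann–Whitney. It does not. Departure must be severe and transformation must fail. After a successful transformation adjusted ANCOVA remains available, because the no-adjustment sentence covers only the last step.
- **The branch may never be used.** A reader might infer that a discrete, bounded questionnaire score is likely to fail the check. The article gives no distribution, mean or floor and ceiling rates, so the probability is unknown.
- **Baseline is not clearly in the planned 4-week model.** The no-adjustment sentence does not name it, and the baseline sentence accompanies the later time points. The like-for-like power comparison is therefore with factor-only ANCOVA, where the loss is small. The larger loss measures what an available covariate could add.
- **Power loss is not general.** It can reverse, as step 5 shows.
- **False positives do not increase.** The error is on the conservative side.
- **The sequence is prespecified.** A reader might infer that the analysts could choose the test to suit the result. Nothing says the check is made by arm or unblinded. The threshold for severe departure, and any estimate reported with the rank test, may properly be left to the analysis plan.

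What remains is an explicit rule, not an omission. In one branch the article itself removes the adjustment that its primary analysis and its allocation scheme call for.

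**Conclusion.** The point holds as a weakness of the last-resort branch. There the primary test ignores the factors used to balance allocation, cannot use baseline fatigue and does not estimate the 0.45 SD mean difference. The loss of the planned mean-difference scale needs no simulation. The conservatism (about 3–4.5% instead of 5%) depends on the factors being prognostic, with an assumed R² of 0.10. The power losses of about 0–4 and about 3–13 points depend on the assumed bounded score, factor R² of 0.03–0.10 and baseline correlation of 0.3–0.5. The documents supply none of these. No stated figure is wrong, and the sample size is reproduced. Severity: recommended improvement, not must-fix.

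**What to change.** In the Analysis section:

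1. Make ANCOVA with arm, the minimisation factors and baseline physical fatigue the primary analysis of 4-week physical fatigue, whatever the distribution. This also settles whether baseline belongs in the primary model.
2. Where residuals are clearly non-Normal, report robust or bootstrap confidence intervals for the adjusted mean difference. The article already plans bootstrapping for costs and QALYs.
3. Make the Mann–Whitney test, or preferably a rank-based or proportional-odds model with the same covariates, a sensitivity analysis.
4. Delete the sentence that removes adjustment, and apply the same rule to the other continuous outcomes.

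The change takes a few sentences and needs no new data or patients. The downsides are slightly more analysis work and possibly lower power than a rank test if the outcome has strong unbounded skew. It should be made before outcome data are examined by arm.
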